### Primary outcomes

The primary objective of this protocol is to determine the additive effect of interactive AR-based telerehabilitation in conjunction with hospital-based physical therapy on passive range of motion (PROM) for patients with adhesive capsulitis 3 months post diagnosis. Therefore, the primary outcome will be the change in PROM of the affected shoulder joint from baseline to 12 weeks after baseline assessment.

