### Sample size calculation

The target sample size was calculated through consultation with an in-hospital statistics team. The primary hypothesis was that there would be a significant difference in the amount of change in PROM before and after 3 months for the digital health care and control groups. The ROM consists of flexion, abduction, external rotation, and internal rotation of the shoulder joint. When the standard deviation of the variation is 18.64, 16.79, 11.22, and 11.65, respectively, and the difference between the two groups variation is expected to be 15, 15, 10, 10, or more, respectively, based on the results of the existing studies [21–25], 35 people per group are required for a significance level of 5% (a significant level of 0.05/4*100% of each hypothesis) and 80% statistical power. Assuming an expected dropout rate of 25%, we require at least 47 participants per group.

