### Statistical analysis

Subject demographics will be calculated using descriptive statistics. Kolmogorov–Smirnov test will be performed to assess the distribution of data. To compare baselines between the two groups, an independent t-test and chi-square test will be conducted. To compare the mean difference, if primary outcome (PROM) data in both groups is found to be normally distributed, we will perform an independent t-test, not Mann-Whitney test. How to handle missing data will be applied depending on distribution of data after study completed.

To investigate the effects of the interventions and differences between groups for secondary outcomes, a mixed effects model or generalized estimating equations will be conducted, with one between-subject factor (group: intervention and control) and one within-subject factor (evaluation time: baseline, 4-week, 8-week, 12-week, 18-weeks, and 24-week follow-ups). All data will be analyzed using IBM SPSS Statistics version 20.0 (Armonk, New York, USA) and a significance level of 5% will be set with a 95% confidence interval.

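### The missing-data method for the primary outcome is to be chosen after completion from the distribution of the data, although the plan allows for 25% dropout

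*Protocol article*

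**What the plan says.** All references are to the protocol article.

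- **Missing data** (Statistical analysis): "How to handle missing data will be applied depending on distribution of data after study completed".
- **Primary outcome** (Primary outcomes): "the primary outcome will be the change in PROM of the affected shoulder joint from baseline to 12 weeks after baseline assessment".
- **Primary test** (Statistical analysis): "if primary outcome (PROM) data in both groups is found to be normally distributed, we will perform an independent t-test, not Mann-Whitney test". Mann-Whitney is implied when normality fails.
- **Longitudinal model** (Statistical analysis): for "differences between groups for secondary outcomes, a mixed effects model or generalized estimating equations will be conducted". It is not offered for the primary outcome.
- **Dropout** (Sample size calculation): "Assuming an expected dropout rate of 25%, we require at least 47 participants per group". The Participants section sets enrolment at 100.
- **Visits** (Study design): outcomes are assessed at baseline and at 1, 2, 3, 4.5 and 6 months.
- **Interim looks** (Data management): none is planned before the study ends.

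**The concern.** The protocol does not leave missing data unmentioned. It says when the method will be picked (after completion) and on what basis (the distribution of the data). An analysis plan that fixed a method in advance would contradict that sentence.

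The basis does not serve the purpose. The shape of the observed values, which the plan examines with a Kolmogorov-Smirnov test, bears on the choice between a t-test and a rank test. It does not show whether absent participants resemble those who stayed. Two trials with identical observed distributions can have harmless dropout in one and strongly selective dropout in the other.

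The document also gives reasons why dropout could differ by arm or by response. One arm has a device installed at home, with remote monitoring and monthly encouragement. The other keeps a log book. Participants may be withdrawn for not following the doctor's instructions (Participant safety and withdrawal), and adherence is what the device is meant to improve (Discussion).

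Two things are at stake. A method chosen late can move the primary result, and nothing stated prevents the choice from being made with group membership known. If no imputation is chosen, the primary contrast also loses everyone without a 12-week value, even those seen earlier.

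**Working it through.** **1. The plan's own figures.** The inputs are from Sample size calculation. The SDs of change, in the order flexion, abduction, external rotation and internal rotation, are given as "When the standard deviation of the variation is 18.64, 16.79, 11.22, and 11.65, respectively". The planned group differences are 15 degrees for flexion and abduction and 10 degrees for both rotations. The level is 0.05/4 = 0.0125 per hypothesis (taken as two-sided), with 80% power.

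n per group = 2 × (2.498 + 0.842)² × (SD/difference)², where the bracket squared is about 11.15:

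- Flexion: 22.30 × (18.64/15)² = 34.4, so 35
- Abduction: 22.30 × (16.79/15)² = 27.9, so 28
- External rotation: 22.30 × (11.22/10)² = 28.1, so 29
- Internal rotation: 22.30 × (11.65/10)² = 30.3, so 31

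The largest is 35, as stated. (A noncentral-t calculation gives 37 for flexion, a small difference of method.) Then 35/(1 − 0.25) = 46.7, so 47, as stated. The sample size is reproduced.

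**2. How many values are at issue.** If the 25% applies at week 12: 0.25 × 94 = 23.5, about 24 participants, or 0.25 × 100 = 25 of the planned enrolment. The inflation to 47 restores precision. It does not protect against bias or against a late choice of method.

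**3. What the primary test can use.** A change from baseline to 12 weeks needs a 12-week value, observed or imputed. A two-sample t-test or Mann-Whitney test takes one number per person. Values at weeks 4 and 8 therefore cannot enter unless an imputation uses them, and none is named.

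**4. Illustration of completer bias (the gap is assumed; it is not in the documents).** With dropout fraction d and gap g between completers and dropouts in one arm:

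arm mean of all randomised = (1 − d) × completer mean + d × dropout mean = completer mean − d × g

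The completer mean is therefore off by d × g. If the other arm has no such gap, the group difference is off by the same amount.

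- g = 4: 0.25 × 4 = 1.0 degree. 1.0/10 = 10%; 1.0/15 = 7%.
- g = 10: 0.25 × 10 = 2.5 degrees. 2.5/10 = 25%; 2.5/15 = 17%.

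On the planning SDs, a 10-degree gap is 10/18.64 = 0.54 SD for flexion but 10/11.65 = 0.86 to 10/11.22 = 0.89 SD for rotation, so the upper end is severe for rotation.

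**5. The same illustration as error rate (also assumed).** Take no true effect, 35 evaluable per group, and intervention-arm dropouts 0.25, 0.5 or 1 SD worse than that arm's completers. Flexion bias is 0.25 × 0.25 × 18.64 = 1.2, 0.25 × 0.5 × 18.64 = 2.3 or 0.25 × 1 × 18.64 = 4.7 degrees. From the noncentral t distribution, rejection at the nominal 1.25% becomes about 1.5%, 2.5% or 7%.

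**The case against.** The other side has several fair points.

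- **A restriction to completers is not stated.** A reader might infer that the primary test is fixed as completers-only. The text does not say so. Because the method is left open, imputation before the t-test remains possible. What stands is the conditional form: only participants with a 12-week value, unless an imputation is chosen later.
- **The sentence does not say the choice follows the results.** A reader might infer that the method will be picked once the group comparison is known. The sentence mentions neither treatment results nor unblinding, and a blinded data review would be compatible with it. What stands is that no such safeguard is stated.
- **The 25% has no time point.** Follow-up runs to 24 weeks, and the allowance might cover all of it. Because it inflates a 12-week comparison, week 12 is the natural reading, but not the only one.
- **The phrase about distribution might mean the pattern of missingness.** That would be a more sensible guide. Even so, observed data cannot rule out that absence depends on the unseen values, and the choice would still be made afterwards.
- **The bias figures rest on an assumed gap in one arm.** That is so. If both arms had equal dropout and the same gap, the biases would cancel. The figures also price completer bias, not the freedom to choose a method.
- **GEE.** Unweighted GEE needs stronger missingness assumptions than a mixed model. It is, however, only one of two options, for secondary outcomes, and removing it is not needed to cure this defect.

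**Conclusion.** The concern holds in this form: the protocol article commits to a data-dependent, after-the-fact choice of missing-data method for the primary outcome, on a basis that cannot justify the choice and without a stated blinding safeguard. This rests on the text alone and on no assumption about dropout.

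The number of participants affected, about 24 of 94 or 25 of 100, depends on reading the 25% as applying at week 12. The bias of 1.0 to 2.5 degrees (10-25% of the 10-degree targets, about 7-17% of the 15-degree targets) is illustrative. It depends on an assumed gap of 4 to 10 degrees in one arm, and its direction depends on which arm has the gap and whether its dropouts would have done better or worse.

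A reader might also infer that the sample size is wrong. It is not: 35 and 47 per group both reproduce.

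The defect bears on the primary conclusion, is cheap to remove now, and cannot be credibly repaired after unblinding. It should be corrected before then.

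**What to change.** Before any comparative or unblinded look, replace **both** the missing-data sentence and the t-test/Mann-Whitney sentence for PROM. Replacing only the first would leave two conflicting primary analyses. The new text should specify:

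1. **Population:** all randomised participants, in their assigned group.
2. **Primary estimate:** for each PROM direction, the 12-week group difference from a mixed model for repeated measures on the week 4, 8 and 12 values, with baseline PROM, centre, visit and group-by-visit.
3. **Fallback:** if PROM is not recorded at weeks 4 and 8, multiple imputation followed by a baseline-adjusted 12-week comparison. The visit schedule needs confirming. Study design says outcomes are assessed at every visit, but the Secondary outcomes section lists active, not passive, range of motion for all follow-ups, and Table 1 is not legible in the text at hand.
4. **Sensitivity:** one delta-adjusted (missing-not-at-random) analysis, which should also cover participants with no follow-up value, since they add no information on change to the model.

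The cost is wording and a little more analysis work. A mixed model is already among the options for secondary outcomes ("a mixed effects model or generalized estimating equations will be conducted"), though the planned version treats baseline as a level of time and has no centre term. The sensitivity analysis may need software beyond the package named. No change is needed to the sample size. No extra visits are needed either, because the fallback covers the case where PROM is not recorded at weeks 4 and 8. With no interim analysis planned, the change can be dated before any comparison.

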**Methods:**

This study presents the protocol of a prospective, multi-center, single-blinded, two-armed randomized controlled trial (RCT). One hundred patients with stage I or II adhesive capsulitis will be recruited at the physical medicine and rehabilitation clinic. Patients will be randomly divided into two groups with 1:1 allocation. The intervention group will receive 3 months of hospital-based physical therapy in conjunction with home-based telerehabilitation. The control group will receive 3 months of hospital-based physical therapy in conjunction with a home-based exercise described in a brochure provided by the hospital. The primary outcome will be the change in passive range of motion (ROM) of the affected shoulder joint from baseline to 12 weeks after baseline assessment. The secondary outcomes will be active ROM, pain measured with the numeric rating scale, shoulder pain and disability index, 36-Item Short Form Survey, EuroQoL-5D-5L, and Canadian Occupational Performance Measure.

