## Methods/design

### Study design

This protocol will be a prospective multi-centered single-blinded two-armed RCT. The study design meets SPIRIT guidelines [13] and the SPIRIT Checklist are attached as Additional file 1. All eligible patients will be informed about this study and invited to participate by the outpatient doctor at the Physical Medicine and Rehabilitation clinic in Republic of Korea. All patients submit informed consent if they agree to participate in the study and principal investigator obtained the informed consent. After randomly divided into two groups with a 1:1 allocation, participants will be assessed in baseline. The intervention group will receive at least 3 months of hospital-based physical therapy in conjunction with home-based telerehabilitation. The control group will receive at least 3 months of hospital-based physical therapy in conjunction with a home-based exercise brochure provided by the hospital. The adhesive capsulitis stage will be evaluated at each follow-up by a physician, and exercises according to the stage will be prescribed. Outcomes will be assessed at the baseline and 1-month, 2-month, 3-month, 4.5-month, and 6-month follow-ups. Deviation of 7–15 days from each evaluation point will be allowed. Outcome measures will be performed by the same assessors, who will be blinded to the group allocation. The flow diagram of the study protocol is shown in Figs. 1 and 2.

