### Secondary outcomes

The secondary objectives of this protocol are to determine the additive effect of interactive AR-based telerehabilitation in conjunction with hospital-based physical therapy on 1) pain intensity; 2) activities of daily living; 3) quality of life; and 4) shoulder disability over time. Therefore, the secondary outcomes will be active ROM, pain measured with the numeric rating scale, shoulder pain and disability index, 36-Item Short Form Survey, European Quality of Life Five Dimensions Five Level Scale, and Canadian Occupational Performance Measure. Along with the RCT, a satisfaction questionnaire (Additional file 3) and safety assessment will be conducted for both the system and equipment.

As secondary outcomes, active range of motion (AROM), pain and disability of the affected shoulder joint, quality of life, and activities of daily living (ADL) will be considered at all follow-up assessments. The satisfaction questionnaire for interactive AR-based rehabilitation will be evaluated only in the intervention group after 12 weeks.

Supine measurements of PROM and AROM of the affected shoulder will be obtained with the participants lying in a supine position. Shoulder forward flexion, abduction, and external and internal rotation with a 90° shoulder abduction will be measured with an electronic goniometer in units of 1°. All ROMs of each participant will be assessed as described by Kelly et al. [14].

The pain intensity at resting and activity will be evaluated by a 11-point Numeric Rating Scale (NRS) [16] for the past week, with 0 and 10 representing “no pain” and “the worst possible pain”, respectively Participants will be asked for an average perceived pain intensity in ADL.

Shoulder pain and disability for the past week will be assessed using the Shoulder Pain and Disability Index (SPADI), consisting of two subscales with a total of 13 items (five items for pain and eight for disability) [17]. Patients will report a level of difficulty performing ADL due to pain and limit of motion. The final score will range from 0 to 130 with a percentage score of 0 indicating less shoulder disability and 100 indicating more shoulder dysfunction.

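### The secondary-outcome model enters baseline as an ordinary level of time, with no baseline adjustment, and so gives up precision that the collected data could supply

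*Protocol article*

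**What the plan says.** The Statistical analysis section of the protocol article gives one model for the secondary outcomes: "a mixed effects model or generalized estimating equations will be conducted". Its terms are "one between-subject factor (group: intervention and control" and "one within-subject factor (evaluation time: baseline, 4-week, 8-week, 12-week, 18-weeks, and 24-week follow-ups". The stated purpose is "To investigate the effects of the interventions and differences between groups for secondary outcomes".

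Under Secondary outcomes, active ROM, pain and disability, quality of life and ADL "will be considered at all follow-up assessments".

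Under Study design, the sequence is given as "After randomly divided into two groups with a 1:1 allocation, participants will be assessed in baseline", and outcomes are collected at baseline and at each of the five follow-ups. Baseline values are therefore planned for everyone, and baseline is listed ahead of the intervention period.

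The article mentions no baseline covariate and no equal-baseline constraint for this model. The primary outcome, change in passive ROM to 12 weeks, is analysed separately by t-test or Mann-Whitney test.

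**The concern.** Baseline precedes treatment, so the true difference between randomised arms at that level is zero. A model that treats baseline as just another visit, with separate arm means, does not use that knowledge. It spends data on estimating a baseline difference that is known in expectation, then carries the noise of that estimate into every change-from-baseline comparison.

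Active ROM, pain, SPADI, SF-36, EQ-5D-5L and COPM all depend on this one sentence. None of them drives the sample size, so their confidence intervals are not protected by design, and avoidable width matters. The six time levels are written out explicitly, so this is a stated modelling choice with a better alternative, not a detail left unsaid.

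**Working it through.** **The plan's own figure.** The article gives no precision or power figure for the secondary outcomes. Its sample size concerns passive ROM. For flexion, at a two-sided level of 0.05/4 = 0.0125 (two-sidedness assumed) and 80% power, n = 2 × (2.498 + 0.842)² × (18.64/15)² ≈ 34.4, so 35 per group. Allowing for 25% dropout, 35/0.75 = 46.7, so 47. Both stated figures reproduce, and neither depends on the secondary model.

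**Inputs for the check**
- Six time levels including baseline, and two groups: Statistical analysis.
- Group size for illustration: 100 participants allocated 1:1 gives 50 per arm; with 25% dropout, 50 × 0.75 = 37.5, taken as 37.
- Assumed, not in the article: equal variance at each visit (set to 1), common correlation r between visits, complete data, and a true 12-week difference of 0.5 SD. The article gives SDs of change for passive ROM only, from which r cannot be recovered, so a range is shown.

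**Precision of the 12-week contrast**
- Unadjusted change from baseline: variance = (2/n) × 2(1 − r).
- Baseline-adjusted: variance = (2/n) × (1 − r²).
- Ratio, adjusted to unadjusted: (1 − r²) / [2(1 − r)] = (1 + r)/2.
- Standard error ratio, unadjusted to adjusted: √[2/(1 + r)].
- Power, two-sided 5%: Φ(0.5/SE − 1.96).

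| r | Variance ratio | Unadjusted SE larger by | Power, unadjusted change | Power, adjusted |
|---|---|---|---|---|
| 0.3 | 0.65 | 24% | 44% | 62% |
| 0.5 | 0.75 | 15% | 58% | 70% |
| 0.7 | 0.85 | 8% | 79% | 85% |
| 0.8 | 0.90 | 5% | 93% | 95% |

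Worked line for r = 0.5: the unadjusted variance is (2/37) × 1.0 = 0.0541, SE 0.2325, so power = Φ(2.15 − 1.96) = 58%. The adjusted variance is (2/37) × 0.75 = 0.0405, SE 0.2013, so power = Φ(2.48 − 1.96) = 70%.

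The ratio (1 + r)/2 is below 1 for every r below 1. The gain shrinks as r rises but does not reverse.

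**If the group main effect were reported instead.** With visits weighted equally, the main effect is (0 + sum of the five follow-up differences)/6, which is 5/6 = 83% of the average over the five follow-ups.

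**The case against.** The strongest reply is that naming one between-subject and one within-subject factor is ordinary shorthand for a two-way design in which group-by-time is the term of interest. The secondary objectives are framed as effects over time, which fits that reading. Baseline as a response level with group-by-time is an established model, is unbiased under randomisation, and retains participants who have only a baseline value. A condensed article may also leave the interaction, the key visit and the contrast to a full protocol or SAP.

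Most of this stands. The absence of a named interaction or contrast is not held against the article here. Nor is baseline in the response wrong in itself: with arm means constrained equal at baseline, it loses none of the precision at issue and still keeps participants without follow-up. What remains is that the model as written has an ordinary group factor over six ordinary time levels and no such constraint.

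A reader might go further and infer that the secondary effects will be biased toward zero. The article does not support that. Shrinkage arises only if the group main effect is the quantity reported, and the text does not say so. The size is also easily overstated. Suppose the effect builds linearly to week 12 and then holds. The six-level average is then (0 + 1/3 + 2/3 + 1 + 1 + 1)/6 = 67% of the 12-week effect, but the five follow-ups alone already average 4/5 = 80%. Baseline accounts only for the factor 5/6 (0.80 × 5/6 = 0.67); the rest comes from comparing a time-averaged effect with a 12-week effect.

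**Conclusion.** The point holds as a loss of precision, not as a demonstrated bias. Read as group-by-time change from baseline, the stated model gives a valid estimate whose standard error is about 24% to 5% larger than that of a baseline-adjusted contrast, for r from 0.3 to 0.8. At r = 0.5 with 37 per arm and a 0.5 SD effect, 12-week power is 58% without adjustment and 70% with it; at r = 0.8 the figures are 93% and 95%, so the benefit may be small for strongly correlated outcomes.

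These figures assume compound symmetry, complete data and a baseline unaffected by treatment. The correlation and the effect size are assumptions, not figures from the article. Only the secondary outcomes are concerned. The type I error is not inflated, and the primary test and sample size stand as they are. This is a worthwhile improvement at no cost, not a flaw that threatens the trial's main conclusion.

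**What to change.** Reword the secondary-outcome paragraph in one of two equivalent directions:

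- Take the five follow-up visits (4, 8, 12, 18 and 24 weeks) as the response, with group, visit, group-by-visit, baseline value and baseline-by-visit as fixed effects; or
- Keep baseline as a response level but constrain the two arms to a common baseline mean.

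In either case, report the adjusted group difference with its 95% CI at 12 weeks, so that the secondary results line up with the primary time point. If the SAP already contains one of these specifications, bring the article's description of the model into line with it.

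The cost is analysis wording only. Baseline is already scheduled for every participant, no new data are needed, and the planned software can fit the covariate form.

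### The 0.05/4 split that sized the trial for four passive-motion hypotheses is not carried into the statistical analysis section, which sets 5% with 95% confidence intervals

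*Protocol article*

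**What the plan says.** Under Primary outcomes, the protocol article states that "the primary outcome will be the change in PROM of the affected shoulder joint from baseline to 12 weeks after baseline assessment". It names no single movement and no composite.

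Under Sample size calculation, the outcome is broken into four: "The ROM consists of flexion, abduction, external rotation, and internal rotation of the shoulder joint". Each movement has its own standard deviation and expected difference, and the level is divided among them: "35 people per group are required for a significance level of 5% (a significant level of 0.05/4*100% of each hypothesis) and 80% statistical power".

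Under Statistical analysis, the primary comparison is a t-test or, if the data are not normal, a Mann-Whitney test. The closing sentence covers everything: it begins "All data will be analyzed using IBM SPSS Statistics version 20.0" and ends "a significance level of 5% will be set with a 95% confidence interval". It neither repeats the four-way split nor treats the primary outcome separately from the secondary outcomes. Nowhere does the article say how many of the four movements must be significant for the trial to count as positive.

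**The concern.** The sample size section pays for protection against multiple testing. The section that says how results will be judged does not mention that protection. An analyst who follows the analysis section literally could report a single movement at p = 0.04 as a positive primary result, which the sizing rule would not allow. The interval level adds a second problem. For any movement with p between 0.0125 and 0.05, the 95% interval excludes zero although the test at the planned level is not significant, and the plan does not say which governs.

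**Working it through.** **Inputs, all from Sample size calculation.** Standard deviations of change are 18.64, 16.79, 11.22 and 11.65. Expected differences are 15, 15, 10 and 10 degrees. The level is 0.05/4 = 0.0125 per hypothesis, power is 80% and dropout is 25%.

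**Step 1: reproduce the plan's figure.** Normal approximation, two-sided: n per group = 2 × (z₁₋α/₂ + z₀.₈₀)² × (SD/difference)².

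At α = 0.0125, 2 × (2.498 + 0.842)² ≈ 22.30. At α = 0.05, 2 × (1.960 + 0.842)² ≈ 15.70.

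| Movement | (SD/difference)² | n at 0.0125 | n at 0.05 |
|---|---|---|---|
| Flexion | 1.544 | 34.4 → 35 | 24.2 → 25 |
| Abduction | 1.253 | 27.9 → 28 | 19.7 → 20 |
| External rotation | 1.259 | 28.1 → 29 | 19.8 → 20 |
| Internal rotation | 1.357 | 30.3 → 31 | 21.3 → 22 |

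The largest value at 0.0125 is 35, the stated figure, and 35/0.75 = 46.7 → 47 also matches. Two-sided 0.05 gives 25 and one-sided 0.0125 gives 30. Of the levels tried, only two-sided 0.0125 gives 35. (Exact t-test power would ask for 37 for flexion, a small matter that does not affect this point.)

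**Step 2: what the 80% refers to.** At 35 per group and 0.0125, power by the same approximation is 0.807, 0.892, 0.891 and 0.863. The 80% is therefore the power for each movement separately, with flexion the limiting one.

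**Step 3: familywise error if 5% is applied to each of four movements and any one suffices.**
- Independent tests: 1 − 0.95⁴ = 0.185.
- With a common correlation among the four test statistics (assumed, because the article gives none; simulation, 1,000,000 draws each): 17.4% at 0.3, 15.5% at 0.5, 13.1% at 0.7, about 11% at 0.8, 9.4% at 0.9 and 5.0% at 1.0.

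**Step 4: the same with the planned split.** Independent tests: 1 − 0.9875⁴ = 0.049. At correlation 0.8 it is 3.2%. The bound is 4 × 0.0125 = 5% whatever the correlation.

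**Step 5: the interval mismatch.** A two-sided test at 0.0125 corresponds to a 1 − 0.0125 = 98.75% interval. For flexion at 35 per group, the standard error is 18.64 × √(2/35) = 4.46 degrees. A 95% interval excludes zero once the observed difference exceeds 1.960 × 4.46 ≈ 8.7 degrees. The test at 0.0125 needs 2.498 × 4.46 ≈ 11.1 degrees. Between those values the interval and the test disagree.

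**The case against.** The strongest reply is that the two sections need not conflict. The sample size section uses the same phrase for the overall level and puts the split in brackets: "for a significance level of 5% (a significant level of 0.05/4*100% of each hypothesis) and 80% statistical power". The 5% in the analysis section can be read in the same way, since it does not say that each movement is tested at 5% and does not withdraw the split. It is also a general closing line, and a condensed article may leave the exact multiplicity wording and the success rule to a fuller document. This stands as far as it goes: the 5% is ambiguous and is not a flat contradiction. It does not rescue the 95% interval, which does not match a 1.25% test on either reading. Nor is this merely a detail left out, because the article does fix a level and an interval for the analysis.

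A reader might also infer that the trial lacks power for passive motion as a whole, because the chance of all four movements being significant at 1.25% is only 0.807 × 0.892 × 0.891 × 0.863 ≈ 55% if they are independent. That does not follow. A rule requiring all four to succeed needs no division of the level. At 5% each, with 35 per group, the power for all four is about 81% with independence and 89% at correlation 0.8. Sizing each hypothesis separately is the natural reading of the plan and is not an error.

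**Conclusion.** The point holds as a mismatch that should be settled before the data are analysed. The sizing rests on 1.25% per movement, the analysis section does not carry that over, and its 95% interval does not match it. The possible consequence is a familywise error of up to 18.5% instead of 5%.

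A reader might take 11% to 19% as the trial's actual false-positive rate, but the document does not support that. The range needs three things that it does not state: 5% applied to each movement, any one movement sufficing, and correlations between 0 and about 0.8. If the planned split is applied, or if all four movements must be significant, the error is at most 5%.

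**What to change.** In the Statistical analysis section, state that:
- each of the four 12-week passive-motion changes is tested at two-sided 0.0125 and reported with a 98.75% confidence interval;
- an effect is claimed only for the movements that meet that level;
- the 5% level with 95% intervals applies to the secondary outcomes.

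In the Sample size calculation, state that the 80% power is per movement.

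The cost is a few sentences. No patients are added, because 35 per group (47 with dropout) already assumes 1.25% per test.

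Holm's procedure is an optional alternative that also controls the familywise error at 5%. Its decisions will not always agree with 98.75% intervals, because later steps can reject at p-values up to 0.05. Under the planned effects at 35 per group, simulation (500,000 draws) gives at least one such disagreement in about 27% of trials at correlation 0, 21% at 0.5 and 15% at 0.8. If Holm is chosen, the plan should say that the adjusted p-values, not the intervals, decide.
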